#### Data analysis

We will evaluate response rates as the number of clinics recruited divided by the number invited and the number of clinicians who agree to participate in the study divided by the number invited. We will also calculate patient recruitment rates as the number of patients recruited per attending physician per day. Audio-recordings of consultations will be collected by the research team at the end of each day and transcribed verbatim. Two trained research assistants will analyze the transcripts independently using the OPTION-5 scale [50–52] to quantify patient/caregiver involvement in the decision-making process during consultations.

We will perform descriptive statistical analyses of all the outcomes and measures. To compare the two study arms on primary and secondary outcomes, we will use hierarchical models to take into account the clustering effects of clinics and clinicians, intervention version, and repeated measures (for outcomes measured three times or more). For clinician-based outcomes, the analysis will take into account the decision considered, clinical site, sociodemographic characteristics of clinicians, and rural/urban localization of the clinic. For patient-based outcomes, the analyses will take into account clinical site, sociodemographic characteristics and dementia severity of patients, and rural/urban localization of the clinic. We will analyze all data following intention-to-treat principles. Quantitative data will be analyzed using the SAS statistical package (version 9.4).

To verify intervention fidelity, we will perform a concurrent analysis of the implementation processes (patient involvement in decision-making).

For each variable analyzed, according to the type of variable (continuous or categorical), the goodness of fit and the assumptions of each model will be assessed. We will analyze all data following intention-to-treat principles. Additionally, if the number of missing data is relatively low, then, in addition to analyzing the data by excluding missing observations, we will also perform a multiple imputation procedure on the full model and verify that results were not affected by missing information.

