### Phase 2: implementation and evaluation of the intervention

#### Study design

In this second phase, we will implement the intervention and evaluate its impact. We will use a two-armed, superiority, parallel-group, clustered RCT with a pre-post evaluation of the impact of the program (Fig. 3). We randomized family medicine clinics to minimize contamination. A biostatistician who is not involved in the main research will use a computer random number generator to randomize the clinics to: (1) immediate exposure to the training program (experimental group); or (2) usual care with delayed exposure to the program (control group). We will monitor implementation throughout the study and will tailor implementation if needed. The protocol of the trial described in this second phase addresses recommendations from the SPIRIT 2013 © checklist (Additional file 1).

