Caregiver of able patient	• Self-reported sociodemographic characteristics of the caregiver (confounding variable) • Caregiver empowerment using the Healthcare empowerment questionnaire [47] (caregiver outcome) • Caregiver burden [48, 49] (caregiver outcome) • Patient quality of life using QoL-AD [50, 51] (patient outcome)
Caregiver (and legal representative) of unable patient	• Self-reported sociodemographic characteristics of the caregiver (confounding variable). • Sociodemographic characteristics of the patient (confounding variable) • Caregiver empowerment using the Healthcare empowerment questionnaire [47] (caregiver outcome) • Caregiver burden [48, 49] (caregiver outcome) • Patient quality of life using QoL-AD [50, 51] (patient outcome)
During consultation	
Audio-recordings of the clinical consultations (OPTION-12)	• Patient involvement in decision-making, using the third-observer OPTION-12 scale [44–46] (process measure)
After clinical consultation (t1)	
Able patient	• Self-reported comfort-level with decision-making measured with the Decisional conflict scale [54, 55] (patient PRIMARY outcome) • Self-reported perceptions of the decision-making processes using the 3-item Collaborate instrument [52, 53] (process measure) • Questions about the clinical visit
Caregiver of able patient	• Self-reported comfort-level with decision-making measured with the Decisional conflict scale [54, 55] (caregiver outcome) • Self-reported perceptions of the decision-making processes using the 3-item Collaborate instrument [52, 53] (process measure) • Questions about the clinical visit
Caregiver (and legal representative) of unable patient	• Self-reported comfort-level with decision-making measured with the Decisional conflict scale [54, 55] (caregiver outcome) • Self-reported perceptions of the decision-making processes using the 3-item Collaborate instrument [52, 53] (process measure) • Questions about the clinical visit
Six months after clinical consultation (t2)	
Able patient	• Patient empowerment using the Healthcare empowerment questionnaire [47] (patient PRIMARY outcome) • Patient quality of life using the QoL-AD [50, 51] (patient outcome)

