Caregiver of able patient	• Caregiver burden using a French-validated questionnaire [48, 49] (caregiver outcome) • Decisional regret [56, 57] • Patient quality of life as perceived by the caregiver QoL-AD [50, 51] (patient outcome) • Caregiver empowerment using the Healthcare empowerment questionnaire [47] (patient PRIMARY outcome)
Caregiver (and legal representative) of unable patient	• Caregiver burden using a French-validated questionnaire [48, 49] (caregiver outcome) • Decisional regret [56, 57] • Patient quality of life as perceived by the caregiver using the QoL-AD [50, 51] (patient outcome) • Caregiver empowerment using the Healthcare empowerment questionnaire [47] (patient PRIMARY outcome)

*C-DB* clinician-decision box, *P-DB* patient-decision box

After the clinicians in the experimental study group have been exposed to e-TUDE and the C-DBs, the research team will start data collection in both the control and experimental study groups. We will meet the patients/caregivers who accepted to participate at the clinic, immediately before their next consultation. They will complete the study entry questionnaires and we will assess baseline levels of patient and caregiver empowerment in healthcare (the primary outcome) [53]. We will also assess caregiver burden [54, 55] as well as patient quality of life using the QoL-AD questionnaire that will be completed by the patient, if s/he is able to do so, and by the caregiver [56, 57].

Then, participating clinicians will audio-record the discussion during the consultation and the recording will be transcribed verbatim by a professional transcriber. This will allow measuring patient/caregiver involvement in the decision-making process using the third-observer OPTION-5 scale.

Right after the consultation, we will ask patients and caregivers their perceptions of the decision-making process during the consultation using the three-item CollaboRATE instrument [58, 59] and their comfort-level with decision-making using the Decisional Conflict Scale [60, 61]. Three months after consultation, we will meet patients and caregivers at their home to ask them to complete again a questionnaire with questions about healthcare empowerment, caregiver burden [54, 55], patient quality of life [56, 57], and decisional regret [62, 63].

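### The Phase 2 model gives the baseline scores for empowerment, quality of life and caregiver burden no stated role in the comparison of arms

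*Protocol article*

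**What the plan says.** Protocol article, Phase 2, Study design, describes a "clustered RCT with a pre-post evaluation of the impact of the program".

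Data collection says that before the consultation "we will assess baseline levels of patient and caregiver empowerment in healthcare (the primary outcome"), and adds: "We will also assess caregiver burden [54, 55] as well as patient quality of life using the QoL-AD questionnaire". Table 3 lists the same three scales again at one follow-up visit, headed "Six months after clinical consultation (t2"). The running text dates that visit differently ("Three months after consultation, we will meet patients and caregivers at their home"). The two timings need reconciling, but on either one each scale is measured twice.

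Data analysis then describes hierarchical models for comparing the arms. They account for clustering by clinic and clinician, for intervention version, and for "repeated measures (for outcomes measured three times or more"). The adjustment list reads: "For patient-based outcomes, the analyses will take into account clinical site, sociodemographic characteristics and dementia severity of patients, and rural/urban localization of the clinic".

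**The concern.** The model description gives two routes by which a t0 score could enter, and neither reaches these outcomes. The repeated-measures route needs at least three measurements, and HCEQ, QoL-AD and burden have two. No patient or caregiver outcome in Table 3 has three. The covariate route lists site, sociodemographics, dementia severity and rural or urban location, but not the baseline value of the outcome. The pre-post label in Study design does not say how the pre measurement is used.

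A baseline score is usually a strong predictor of the same score at follow-up. Leaving it out gives a wider confidence interval than the data allow. With six clinics randomised, a chance difference between arms at t0 is a practical possibility, and part of it carries into an unadjusted t2 comparison. The Power calculation section answers the small number of clusters only with an expectation that the groups will be similar, supported by OPTION scores and not by empowerment scores.

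**Working it through.** **Inputs (Power calculation and Table 4, scenario 3):** 162 patients, taken as 81 per arm; six clinics with a mean of 27 patients; SD 2.46; ICC 0.02; difference 1.476; 5% significance level, taken as two-sided. **Assumption:** t0–t2 correlation ρ of 0.3, 0.5 or 0.7, since the article gives none.

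**1. The plan's own power.** Design effect = 1 + (27 − 1) × 0.02 = 1.52. Adjusted SD = 2.46 × √1.52 = 3.03 (Table 4 prints 2.98). Standard error of the arm difference = 3.033 × √(2/81) = 0.477 points, or 0.194 SD. A two-sided t-test on 160 df then has power 86.8%; with the printed 2.98 it is 88.0%. The stated 88% thus reproduces as a two-group comparison with cluster inflation and no baseline correlation.

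**2. Adding t0 as a covariate.** The variance is multiplied by (1 − ρ²), taking the same correlation between and within clinics and comparing with a model that has no other covariates.

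| ρ | Variance cut | SE (points) | Power, 160 df | Power, 4 df |
|---|---|---|---|---|
| none | – | 0.477 | 87% | 65% |
| 0.3 | 9% | 0.455 | 90% | 68% |
| 0.5 | 25% | 0.413 | 94% | 76% |
| 0.7 | 49% | 0.340 | 99% | 89% |

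The last column uses clinic-level degrees of freedom (6 − 2 = 4). It shows that the gain does not depend on the plan's choice of df.

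**3. What the gain is worth in patients.** With six clinics fixed, the variance is proportional to (1 − 0.02)/m + 0.02 for m patients per clinic. At m = 27 this is 1.52/27 = 0.0563. A 25% cut gives 0.0422, so m = 0.98/(0.0422 − 0.02) ≈ 44. That is 44 per clinic instead of 27, about 63% more.

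**4. Chance imbalance.** If the t0 score has the same SD and ICC, the t0 difference between arms also has a standard error of 0.194 SD. A gap of 0.3 SD or more in either direction has probability P(|Z| > 0.3/0.194) ≈ 12%. The unadjusted t2 difference then shifts by ρ × 0.3 × 2.46 points:
- ρ = 0.3: 0.22 points (15% of 1.476)
- ρ = 0.5: 0.37 points (25%)
- ρ = 0.7: 0.52 points (35%)

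**5. Change score instead.** Its variance factor is 2(1 − ρ): 1.4, 1.0 and 0.6 for the three correlations. It is worse than ignoring t0 when ρ is below 0.5, equal at 0.5, and always less precise than covariate adjustment in this range. Reading pre-post as a simple difference would therefore not secure the gain.

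**The case against.** The strongest objection is that this is a condensed article whose analysis plan is not shown. The adjustment list is not declared exhaustive, and the form in which a baseline enters is often left to the analysis plan. The pre-post label and the collection of baseline levels suggest that the authors meant to use t0; the three-measurement rule may only mean that two-point outcomes need no repeated-measures structure. This stands in part: that t2 is analysed alone is an inference. But the article goes beyond silence. It publishes a covariate list and a numerical threshold, and a primary outcome falls outside both.

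A reader might infer that the comparison is biased, that every primary analysis ignores a baseline, or that t0 and t2 would be entered as independent rows. The documents support none of these. Randomisation keeps a t2-only comparison valid. The Decisional Conflict Scale, also labelled primary, is first measured after the consultation and has no baseline to use. No model with independent rows is proposed.

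Two further objections stand. First, the gains above are measured against a model without covariates, while the plan already adjusts for dementia severity and sociodemographics, which may capture some of the same variation. Second, t0 is not a clean pre-intervention value. Data collection starts in both arms only after the experimental clinicians have had e-TUDE and the clinician Decision Boxes, so earlier contact with a trained clinician could already have moved a t0 score.

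**Conclusion.** The point holds as a gap between the stated model and the stated design. As Data analysis is written, the t0 values of HCEQ, QoL-AD and caregiver burden have no stated role in comparing the arms. The consequence is lost efficiency and weaker protection against chance imbalance, not an invalid analysis.

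For HCEQ the available gain is a variance reduction of at most 9% to 49%, with power rising from about 87% to between 90% and 99% on the plan's own method. These figures rest on an assumed correlation of 0.3 to 0.7, on equal arms, and on the plan's SD and ICC. They are upper limits in so far as the listed covariates already explain part of the outcome. The protection against imbalance also requires that t0 was not itself affected by the intervention. For QoL-AD and burden the same reasoning applies, but the article gives no SD or ICC from which to size it.

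**What to change.** In Phase 2, Data analysis, state that t2 HCEQ, QoL-AD and caregiver burden are each analysed in the hierarchical model with the same respondent's t0 score on that scale as a covariate, in addition to the covariates already listed. Keep the repeated-measures structure for outcomes that do have three or more measurements. Report the analysis without t0 as a sensitivity analysis. Align the pre-post wording in Study design with this.

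The cost is one covariate per model and a sentence of text. No new data are needed, and the article reports that Phase 2 data were still being collected.

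The downside is that, if the intervention had already shifted t0 in the experimental arm, adjustment would absorb part of the effect. A difference between the adjusted and unadjusted results can flag this, but cannot separate it from chance imbalance. The text should say so.

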#### Data collection

Clinicians from the clinics allocated to the experimental group will complete questionnaires after their training with e-TUDE and after receiving each C-DB (Table 3). These data will allow us to evaluate whether the intervention changes clinicians’ perceptions of being able to adopt shared decision-making using the novel ICanSDM scale ([name], personal communication), the role they prefer during the clinical decision-making process, and their intention to engage senior patients living with dementia and their caregivers in decision-making about a choice of health options.

**Table 3 Tab3:** Phase two (RCT) data collection steps, outcomes, processes measures, and confounding variables

Step	Outcomes (measures)
Clinician baseline, at recruitment (t0)	
Clinician, at recruitment	• Self-reported sociodemographic characteristics (confounding variables) • Self-reported interest for each of the topics addressed in the C-DB on a 1–10 visual analogue scale
Clinician, during professional training (only for those allocated to the experimental group)	
Before e-TUDE	• Role preference scale [63] • Perceptions of being able to adopt shared decision-making using the ICanSDM scale • Intention to engage senior patients living with dementia and their caregivers in decision-making about choosing a health intervention, based on the TPB [37, 38]
After e-TUDE	• Satisfaction with e-TUDE (1–5 smiley face scale) • e-TUDE usability based on the *Technology Acceptance Model* (TAM-2) [64–66]
After reception of each C-DB	• Satisfaction with DB (1–5 smiley face scale) • DB usability based on the *Technology Acceptance Model* (TAM-2) [64–66] • Value of the evidence presented in the P-DB, measured using the clinician version of the IAM [43, 67]
When training is completed	• Role preference scale [63] • Perceptions of being able to adopt shared decision-making using the ICanSDM scale • Intention to engage senior patients living with dementia and their caregivers in decision-making about choosing a health intervention, based on the TPB [37, 38]
Patient baseline, before clinical consultation (t0)	
Able patient	• Sociodemographic characteristics of the patient: self-reported by the patient (confounding variable) • Patient empowerment using the Healthcare empowerment questionnaire [47] (patient PRIMARY outcome) • Patient quality of life using the French-validated QoL-AD [50, 51] (patient outcome)

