#### Power calculation

We estimate that a sample of 162 patients will allow us to detect a mean difference of 1.476 in their empowerment in healthcare (corresponding to an effect size of 0.6) between our two groups. Assuming a standard deviation of 2.46 and an ICC (intraclass correlation coefficient) of 0.02, such a sample would give us a statistical power of 88% to detect the proposed mean difference at a significance level of 5% (Table 4). To account for an attrition and missing data rate of 10%, we have set a target of 180 patients. A previous study conducted by our research team yielded an ICC of 0.02 in a similar setting when measuring the frequency with which clinicians prescribed antibiotics after training in SDM [64]. We estimate that this convenient sample of 162 patients post intervention will allow us to detect a mean difference of 2.6% (SD = 4.8, Cohen’s D = 0.55) in decisional comfort (Decisional Conflict Scale) considering an ICC of 0.02 at a significance level of 0.05 and with a power of 80%.

**Table 4 Tab4:** Effect of study length on the power of the study

Scenario	Estimated power	Threshold of statistical significance	HCEQ Standard Deviation	Minimum detectable difference (Cohen’s effect size of 0.6)	Intra-cluster correlation	Adjusted standard deviation	Number of clusters (clinics)	Totalsample size	Study length (months)	Mean number of patients per clinic
1	0.519	0,05	2.46	1.476	0,02	2.65	6	54	1	9
2	0.76	0,05	2.46	1.476	0,02	2.85	6	108	2	18
3	0.88	0,05	2.46	1.476	0,02	2.98	6	162	3	27
4	0.92	0,05	2.46	1.476	0,02	3.21	6	216	4	36
5	0.948	0,05	2.46	1.476	0,02	3.37	6	270	5	45
6	0.963	0,05	2.46	1.476	0,02	3.53	6	324	6	54

Despite a relatively small number of clusters (six clinics to be randomized), we are confident that practice variation will be low enough to allow similar groups at baseline. Indeed, a recent systematic literature review reports rather uniform and low adoption of shared decision-making in the general practices in Canada, with two studies reporting OPTION scores of 24 ± 8 on a scale of 0–100 for one study (*n* = 152) and 19 ± 7 (*n* = 41) for the other.

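### The stated model makes no use of the baseline HCEQ, QoL-AD and caregiver-burden scores, and its site, rural/urban and dementia-severity terms need a defined role or source

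*Protocol article*

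**What the plan says.** The Phase 2 Study design section describes a "clustered RCT with a pre-post evaluation of the impact of the program". Under Data collection, just before the consultation, "we will assess baseline levels of patient and caregiver empowerment in healthcare (the primary outcome") are recorded. Table 3 lists the same at t0: "Patient empowerment using the Healthcare empowerment questionnaire [47] (patient PRIMARY outcome"). It places HCEQ, QoL-AD and caregiver burden at t0 and again at t2, and at no other time. The Decisional Conflict Scale, which Table 3 also labels primary for patients, appears only at t1.

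The Data analysis section then fixes the comparison of arms: "we will use hierarchical models to take into account the clustering effects of clinics and clinicians", together with intervention version and "repeated measures (for outcomes measured three times or more"). The covariates are given separately: "For patient-based outcomes, the analyses will take into account clinical site, sociodemographic characteristics and dementia severity of patients, and rural/urban localization of the clinic".

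On comparability of the arms, the Power calculation section says of the six clinics that "we are confident that practice variation will be low enough to allow similar groups at baseline".

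**The concern.** The t0 scores have no route into the stated arm comparison. They are not covariates, and an outcome measured twice does not meet the rule of three or more measurements. In Table 3, no outcome that could compare the arms is measured three times, so that rule brings in none of them. The measures repeated after each C-DB are taken in the experimental group only.

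This costs precision in a trial with six randomised units, where little else can recover it. It also leaves chance differences between clinics in the outcome itself unadjusted.

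Three of the terms that are listed raise their own questions. Clinical site is named in addition to clinic clustering, and its role is not stated. Rural/urban is a clinic-level term that uses up scarce between-clinic information. Dementia severity has no measure in Table 3, whose title says that it covers confounding variables.

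**Working it through.** **Inputs from the Power calculation section and Table 4.** Difference 1.476, SD 2.46, ICC 0.02, six clinics, 27 patients per clinic, 162 patients, 5% significance. Assumed here: a two-sided test and three clinics (81 patients) per arm.

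**The plan's own figure.** Design effect = 1 + (27 − 1) × 0.02 = 1.52. Adjusted SD = 2.46 × √1.52 = 3.03 (Table 4 prints 2.98). SE = 3.03 × √(2/81) = 0.477. Ratio = 1.476/0.477 = 3.10. Power is 87.2% by the normal approximation, and 88.0% by t on 160 df with the printed 2.98. The stated 88% reproduces. It neither uses nor depends on baseline adjustment.

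**Same ratio, referred to the number of clinics.** Six clinics less two arm means leave 4 df. Critical t is 2.776 and noncentral-t power is 64.5%. This is the reference for what follows.

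**Adding the t0 score.** The t0-t2 correlation r is not in the article, so a range is shown. Two bounds:
- Upper: all variance shrinks by 1 − r², so SE = 0.477 × √(1 − r²).
- Lower: only within-clinic variance shrinks, so SE = √{2 × [0.02 × 2.46²/3 + 0.98 × 2.46² × (1 − r²)/81]}.

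| r | SE, lower to upper bound | Ratio | Power, 4 df |
|---|---|---|---|
| 0 | 0.477 | 3.10 | 64.5% |
| 0.3 | 0.463 to 0.455 | 3.19 to 3.25 | 67-68% |
| 0.5 | 0.436 to 0.413 | 3.38 to 3.58 | 72-76% |
| 0.7 | 0.394 to 0.340 | 3.74 to 4.34 | 80-89% |

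**Clinical site.** With site fixed, the design matrix has an intercept, arm and five site indicators: 7 columns, rank 6. Arm is a linear combination of the site columns, so its effect cannot be estimated. With site as the random clinic level there is no such problem.

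**Rural/urban.** Intercept, arm and rural/urban give 3 columns, rank 3, so arm is estimable. The term is aliased with arm only if it splits exactly by arm: 2 of 20 patterns with three rural clinics, none with one or two. Otherwise it leaves 3 df (critical t 3.182) and multiplies the arm variance by 1.0 to 2.0. Without baseline adjustment, power is:
- 55.7% if balanced by arm (factor 1.0);
- 51% with three rural clinics split two and one (factor 1.125);
- 48% with one rural clinic (factor 1.25);
- 33% if both of two rural clinics fall in one arm (factor 2.0).

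**Dementia severity.** Table 3 records sociodemographic characteristics of patients at t0 and no severity measure. The Phase 2 Data collection text adds none.

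**The case against.** The article calls the design pre-post, so a use of t0 is plainly intended, and whether through a change score or covariance adjustment is commonly left to a fuller document. That would answer silence. The article is not silent: it states a covariate list and a repeated-measures rule, and together these exclude t0.

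A reader might infer that the clinic-level terms are aliased with arm and that the model cannot estimate a treatment effect. The article does not support that. It specifies hierarchical models with clinic clustering and never says that site is fixed, so site may simply be the random clinic level. Rural/urban is not aliased with arm in general. Intervention version is not defined, so nothing can be concluded from it.

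A reader might also set the two OPTION means cited under Power calculation (24 and 19, with SDs of 8 and 7) against the 0.6 SD effect and infer an imbalance of that order. That does not follow: these are separate studies of an observer-rated process measure, not HCEQ. On the plan's own ICC, the SE of a chance difference between arms is √{(2/3) × (0.02 + 0.98/27)} = 0.19 SD, so a 0.6 SD imbalance would be about 3 SE.

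The strongest objection concerns the remedy. "After the clinicians in the experimental study group have been exposed to e-TUDE and the C-DBs, the research team will start data collection" in both arms, so t0 follows randomisation and training. If a patient had already met a trained clinician, t0 may carry some intervention effect and adjustment would remove part of it. An unadjusted analysis cannot fully separate this from chance imbalance. This stands as a small downside, limited by t0 being taken immediately before the study consultation.

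**Conclusion.** The point holds for HCEQ, QoL-AD and caregiver burden: as written, the model uses none of their t0 scores. It does not apply to the Decisional Conflict Scale, which has no t0 value.

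On 4 cluster df the gain in HCEQ power is about 3 to 4 percentage points at r = 0.3, 7 to 12 at r = 0.5 and 15 to 25 at r = 0.7. It rests on the assumed correlation, on three clinics per arm, and on the plan's SD and ICC. It does not make the stated 88% wrong.

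Of the listed terms, the role of site is ambiguous and would be fatal only if fixed. Rural/urban costs one of about four cluster df. Dementia severity is a covariate without a listed source. These should be corrected, but they do not show that the planned analysis is unworkable.

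**What to change.** For HCEQ, QoL-AD and caregiver burden, state the main analysis as the t2 score on arm and the t0 score of the same outcome, with clinic and clinician as random effects. Keep an analysis without t0 as a sensitivity analysis, and say that t0 is taken after randomisation and after experimental-arm clinicians were trained, so a gap between the two analyses has more than one possible explanation.

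State that clinical site enters only as the random clinic effect. Move rural/urban to a sensitivity analysis. Either drop dementia severity or name its source and add it to Table 3.

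The cost is wording, with no change to design or sample size. The exception is dementia severity: recruitment is complete and Phase 2 data are being collected, so keeping it would probably mean chart extraction, a small extra cost.

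### The multiple-imputation check is tied to low missingness, so it lapses when missing follow-up data are substantial

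*Protocol article*

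**What the plan says.** The rule stands at the end of the Phase 2 Data analysis section of the protocol article: "if the number of missing data is relatively low, then, in addition to analyzing the data by excluding missing observations, we will also perform" multiple imputation. Its stated purpose is to confirm that missing information has not affected the results. No value is given for the point at which missingness stops being low, and no other method is named for that case.

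Three other statements bear on it:

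- The same section says twice: "We will analyze all data following intention-to-treat principles".
- It specifies hierarchical models, but accounts for "repeated measures (for outcomes measured three times or more" only.
- The Power calculation section deals with loss through the sample size: "To account for an attrition and missing data rate of 10%, we have set a target of 180 patients".

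**The concern.** The condition governs the imputation, not the exclusion. Read literally, the check runs when few data are missing, where it is least likely to change anything, and is not called for when many are missing. Because the trigger has no number, whether it is met would be decided with the data in view.

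Informative loss is plausible for the later outcomes. Table 3 collects patient empowerment only from able patients, at t0 and again at t2. A patient who loses the ability to answer between those visits has no patient score at t2, so missingness can follow decline. The 10% allowance protects power; it does nothing about bias. What is at stake is whether a treatment difference based on the patients still answering at t2 would be reported with any stated check on those who are not.

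**Working it through.** **1. The plan's own figures.** The inputs are in the Power calculation section and Table 4: "We estimate that a sample of 162 patients will allow us to detect a mean difference of 1.476 in their empowerment in healthcare", and "Assuming a standard deviation of 2.46 and an ICC (intraclass correlation coefficient) of 0.02".

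- Attrition: 162 / (1 − 0.10) = 180, as stated.
- SD inflated for 27 patients per clinic: 2.46 × √(1 + 26 × 0.02) = 3.033.
- Power by normal approximation, two-sided 5% assumed, 81 per arm: 0.872. With the 2.98 printed in Table 4 it is 0.883. Both agree with the stated 88%.

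The allowance and the power therefore reproduce on the plan's own method. They are not at issue here.

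**2. What the rule yields in each case.**

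| Missingness | Excluding missing observations | Multiple imputation |
|---|---|---|
| Relatively low | stated | stated, as a check |
| Not low | stated | not called for; no alternative named |

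**3. Whether the main model fills the gap.** A likelihood model over all visits could use partial records. The repeated-measures structure is restricted to outcomes measured at least three times, however. In Table 3, empowerment, quality of life and caregiver burden are each scheduled twice (t0 and t2), and decisional regret once. A patient without a t2 value therefore drops out of the t2 comparison. The patient covariates listed (site, sociodemographics, dementia severity, rural or urban location) do not name the t0 score or the caregiver scores, although both are collected.

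**4. Which outcomes are affected.** The Decisional Conflict Scale, labelled a patient primary outcome in Table 3, is completed right after the consultation, so later dropout does not reach it. The exposed outcomes are those collected months later. Table 3 puts that visit at six months and the Data collection text at three.

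**5. Illustrative size.** Let p1 and p0 be the proportions lost by arm, and Δ the amount by which lost patients score below observed ones, the same in both arms. In each arm the observed mean equals the true mean + p × Δ, so

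bias in the unadjusted difference = (p1 − p0) × Δ.

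The loss rates and Δ are assumptions; only 2.46 and 1.476 come from the article.

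| Loss by arm | Δ = 0.5 SD (1.23) | Δ = 1 SD (2.46) |
|---|---|---|
| equal | 0 | 0 |
| 20% v 10% | 0.10 × 1.23 = 0.12 (8% of 1.476) | 0.10 × 2.46 = 0.25 (17%) |
| 30% v 15% | 0.15 × 1.23 = 0.18 (12.5%) | 0.15 × 2.46 = 0.37 (25%) |

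For scale, the standard error of the difference at the planned 162 patients is 3.033 × √(2/81) = 0.48. The direction depends on which arm loses more: the mean of that arm is raised more.

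**The case against.** The case on the other side has real force.

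- **The clause governs a supplementary check.** It does not alter the main model, the sample size or the power. At the planned 10% the check would probably run; a 30% v 15% loss averages 22.5% with equal arms, more than twice that rate. This stands and limits the importance of the point.
- **Imputation may recover little.** When only the outcome is missing and the imputation uses the same covariates as the adjusted model, it gives essentially the adjusted complete-case answer. If loss depends on the unseen outcome, imputation under missing at random does not remove the bias. Both statements are right. The figures above are shifts in unadjusted means, not amounts that imputation would recover. The gain comes from information outside the main model, here the t0 and caregiver scores.
- **The silence about high missingness may be filled elsewhere.** A reader might infer that nothing but complete-case results will ever be reported. The article does not say so; it only states no other analysis. The lack of a cut-off would, on its own, be detail for an analysis plan. The direction of the condition is different: it is a stated rule, and a plan that followed it would inherit it.
- **Imputation is less trusted when much is missing.** That may be the thinking behind the condition, but it would call for a named alternative, and there is none.
- **Intention to treat.** A reader might infer that excluding missing observations contradicts the intention-to-treat statement. That goes too far. The article commits to principles, which at the least means analysis by allocated arm, and excluding missing observations does not flatly contradict that.

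**Conclusion.** The point holds as a fault in a stated rule. The imputation check is attached to the condition under which it is least informative, and for substantial missingness the article states only the analysis that excludes missing observations. Nothing else in the article corrects this for outcomes measured twice. It concerns mainly empowerment and the other months-later outcomes.

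The article does not fix the size of the consequence. A shift of 0.18 to 0.37 points rests on an assumed 30% v 15% loss, an assumed deficit of 0.5 to 1 SD that is equal in both arms, and no covariate adjustment. Under equal loss it is zero. It would be wrong to conclude that the trial will be biased by this amount, or that imputation alone would put it right.

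**What to change.** Delete the low-missingness condition. Run the multiple imputation whatever the missing rate, with a model that respects clustering by clinic and includes arm, the t0 score and the caregiver scores already collected, besides the planned patient covariates. Report it beside the analysis excluding missing observations. Because imputation under missing at random does not address outcome-dependent loss, add a delta-adjusted sensitivity run if loss exceeds the planned 10%. Which analysis is primary can stay with the sponsor's statistician.

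The cost is a change of wording and modest programming, with no new data. One limit should be acknowledged: with six clinics the between-clinic variance in the imputation model will be imprecisely estimated. The Recruitment status section reports Phase 2 data collection as still under way, so as of that report the change could be made before analysis.
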